## D.2 Exclusion Criteria

- 1. Describe the criteria that define who will be **excluded** in the study as a numbered list:
- Unwillingness or inability to provide informed consent by the patient or substitute decision maker for healthcare decisions
- Patients with known, moderate or greater, regurgitant valvular disease (i.e. aortic regurgitation, mitral regurgitation, tricuspid regurgitation).

1. Describe in detail how the eligibility criteria will be assessed and satisfied (e.g., medical record review, physical examination):

Medical record review and discussion with patient

1. State who will determine eligibility. Note that those who are designated to determine eligibility must have appropriate training, expertise, and oversight, for example a physician PI or Co-I on a biomedical study:

- The primary and co-investigators (i.e. Drs. [name], [name], and [name]). .

1. *Can study subjects participate in another research study while participating in this research study:*

Yes  No

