## B.1 Background and Rationale

The role of ultrasound in bedside patient assessment has expanded drastically over the past two-decades. In particular, technological advances in recent years – which have considerably reduced the size and cost of ultrasound devices – have expanded the availability of ultrasound beyond the confines of formal diagnostic laboratories.^1–3^ Due to the significant difficulty, and unreliability, of cardiovascular assessment, bedside cardiac ultrasound – coined focused cardiac ultrasound (FoCUS) – is increasingly being incorporated into the routine evaluation for cardiac pathology.^3,4^

While several societal guidelines have outlined the recommended elements of a FoCUS assessment, perhaps none is most important than evaluation of left ventricle (LV) systolic function.^5–8^ Formal evaluation of LV systolic function, with transthoracic echocardiography (TTE), is assessed through measuring the difference between the end-diastolic and end-systolic volumes of the LV, and dividing by the end-diastolic volume – thereby calculating the left ventricular ejection fraction (LVEF).^9^ Calculating LV volumes through 2D linear measurements (i.e. Teichholz and Quinones methods) are not recommended due to the potential for significant inaccuracy as a result of the geometric assumptions required with these methods. Rather, the American Society of Echocardiography recommends that, when using 2D echocardiography, LV volumes are measured using the biplane method of disks summation (modified Simpson’s rule), whereby the LV cavity is traced in the apical four- and apical two-chamber views at end-systole and end-diastole.^9^ These volume measurements can then be applied, as described above, to calculate the LVEF, as well as to estimate the stroke volume and cardiac output. Hemodynamic parameters such as stroke volume and cardiac output can also be obtained from invasive right heart catheterizations. During a right heart catheterization, pressure measurements are obtained via a pulmonary artery catheter inserted via the right jugular vein.

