# Enrollment and Withdrawal

## D.1 Inclusion Criteria

- 1. Describe the criteria that define who will be **included** in the study as a numbered list:
- All patients who are cared for at Tufts Medical Center and:
  - Provide informed consent
  - Age greater than or equal to 18 years old
  - Undergo bedside FoCUS examination with the KOSMOS portable ultrasound device
  - Have had a TTE within 30 days, or have had a TTE ordered by the primary treating team and/or have had/are scheduled for a right heart catheterization with calculation of stroke volume and cardiac output

##

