### D.4.1 Local Recruitment Methods

Describe the following attributes of the recruitment plan for the local Tufts site:

1. When, where, and how potential subjects will be recruited:

Potential subjects will be screened for potential recruitment by the study investigators This will occur when patients are admitted to the inpatient medical, surgical or intensive care units at Tufts Medical Center and/or when they present to TMC for an echocardiogram and/or right heart catheterization. Once screened for possible inclusion the study team will approach the patient for inclusion in the study.

1. Source of subjects (for example, patient population, local community, etc.): Subjects presenting to TMC for an echocardiogram and/or right heart catheterization and those admitted to TMC.
2. Methods that will be used to identify potential subjects: Physician referral and chart review
3. If print and media advertisements will be used, specify when, where, how long and frequency of the advertisements that will be published/aired:       or  N/A
   1. Check to confirm that any necessary permission will be obtained for posting/airing these (for example, permission to post a flyer on a bulletin board).
4. If recruitment material is being mailed or otherwise distributed, submit the proposed material and describe where/how the distribution list will be obtained:       or  N/A
5. Describe how the recruitment methods described will be effective in attracting the targeted subject population: The target population is patients who recently underwent or are scheduled to undergo an echocardiogram and/or right heart catheterization. By screening patients scheduled for these tests we will be able to efficiently identify potential subjects for recruitment.

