## I.1 Study Endpoints

1. Describe the primary and secondary study endpoints:

The primary outcome of interest is the overall diagnostic accuracy of the automated LVEF, stroke volume, and cardiac output computation as compared to either TTE (for LVEF assessments) or right heart catheterization (for stroke volume and cardiac output assessments).

1. Describe any primary or secondary safety endpoints:

- Time to LVEF acquisition with FoCUS

##

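### Patients with an LV assist device, an LV pump or a significant atrial-level shunt stay in the stroke volume and cardiac output comparison, where device and catheter can differ by physiology

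*Protocol*

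**What the plan says.** I.1 makes the accuracy of automated LVEF, stroke volume and cardiac output the primary outcome. The reference for the last two is "right heart catheterization (for stroke volume and cardiac output assessments").

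B.1 describes how LV cavity volumes are traced on echocardiography and adds: "These volume measurements can then be applied, as described above, to calculate the LVEF, as well as to estimate the stroke volume and cardiac output". It describes the catheterization in these terms: "pressure measurements are obtained via a pulmonary artery catheter inserted via the right jugular vein".

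Entry to this component is wide. D.1 admits adults who "have had/are scheduled for a right heart catheterization with calculation of stroke volume and cardiac output". D.4.1 recruits, among others, patients "admitted to the inpatient medical, surgical or intensive care units at Tufts Medical Center".

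D.2 has two exclusions. One concerns consent: "Unwillingness or inability to provide informed consent by the patient or substitute decision maker for healthcare decisions". The other is the only cardiac one: "Patients with known, moderate or greater, regurgitant valvular disease (i.e. aortic regurgitation, mitral regurgitation, tricuspid regurgitation"). I.2 repeats it after enrollment: everyone enrolled is analysed, and the single exception is moderate or greater regurgitation found later. Intracardiac shunt and mechanical support of the LV are not mentioned anywhere in the protocol.

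**The concern.** Output computed from LV volumes and output from a right heart catheter are the same quantity only if two conditions hold. All the volume leaving the LV cavity must be forward flow ejected by the LV, and flow through the right heart must equal flow through the left. Regurgitation can break this, and the protocol removes it both at entry and after enrollment. An LV assist device or pump, or a significant atrial-level shunt, can break it too, and nothing removes those patients.

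For such a patient, a device that measured LV volumes perfectly could still disagree with the catheter, and the disagreement would be booked as device error. Two of the three primary measures are exposed, in the smaller of the two components. LVEF against TTE is not affected, because both methods there describe the same chamber.

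**Working it through.** **1. The plan's own figure.** I.2 gives 35 evaluable patients from 90% agreement and a 10% margin. With n = z² p(1 − p)/d² and two-sided 95% confidence (assumed; not stated):

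- Output: 3.8415 × 0.90 × 0.10 / 0.10² = 34.57, rounded up to 35.
- LVEF, as a cross-check (95%, 5% margin): 3.8415 × 0.95 × 0.05 / 0.05² = 72.99, rounded up to 73.

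Both reproduce. The point concerns who is in the 35, not the arithmetic.

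**2. Tracing one patient through the text.** Take an adult with an LV assist device, scheduled for right heart catheterization, scanned with KOSMOS, consenting, and without known moderate regurgitation.

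- D.1: meets every inclusion criterion.
- D.2: meets neither exclusion.
- I.2: does not fall under the one post-enrollment exception, so is analysed.

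The same holds for a patient with a significant atrial-level shunt.

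**3. Whether the two measurements separate.**

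- *LV assist device or percutaneous LV pump.* Venous return crosses the right heart and is seen by the catheter. Part of it then reaches the aorta through the pump and not by LV ejection, so the difference between end-diastolic and end-systolic LV volume need not equal it.
- *Atrial-level shunt.* Blood crossing between the atria passes through one ventricle and not the other, so pulmonary flow and LV output differ. Whether the reported catheter figure follows one or the other depends on the method (thermodilution or Fick) and, for Fick, on where venous blood is sampled. The protocol does not state the method.

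**4. Scenario on the difference scale.** The documents give no SD, no gap and no count, so all three are assumptions: SD of cardiac output differences 0.8 L/min in comparable patients; a fixed gap g of 2 or 3 L/min, same sign, in affected patients; k affected among 35. With p = k/35, SD = √(0.8² + p(1 − p)g²), half-width of the limits = 1.96 × SD, and bias shift = p × g. With k = 0 the half-width is 1.96 × 0.8 = 1.57 L/min.

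| k | g (L/min) | SD | Half-width | Widening | Bias shift |
|---|---|---|---|---|---|
| 1 | 2 | 0.867 | 1.70 | 8% | 0.06 |
| 2 | 2 | 0.925 | 1.81 | 16% | 0.11 |
| 4 | 2 | 1.022 | 2.00 | 28% | 0.23 |
| 1 | 3 | 0.943 | 1.85 | 18% | 0.09 |
| 2 | 3 | 1.061 | 2.08 | 33% | 0.17 |
| 4 | 3 | 1.245 | 2.44 | 56% | 0.34 |

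With an SD of 1.0 L/min and gaps of 1.5 to 4.0 L/min, the widening is 3% to 20% for one patient, 6% to 36% for two and 11% to 62% for four.

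**5. Scenario on the agreement scale used for the sample size.** If every affected patient counted as a non-agreement, expected agreement would be 0.90 × (35 − k)/35: 87.4% for one, 84.9% for two and 79.7% for four. Each patient costs about 2.6 points, against a planned margin of 10.

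**The case against.** The strongest reply is that the stated aim is accuracy in a real-world clinical setting, so broad entry is a deliberate choice. This stands as a reason to enrol such patients. It does not make the catheter a valid reference for LV-volume output in them, and the protocol has already given up some breadth by removing regurgitation.

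Five further points stand and limit the finding.

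- **Scope of the physiology.** A reader might infer that all mechanical support and any intracardiac shunt cause the problem. The reasoning does not support that. Veno-arterial extracorporeal support bypasses the pulmonary artery as well as the LV, and veno-venous support bypasses neither ventricle. A right-sided assist device does not bypass the LV. With a left-to-right ventricular-level shunt, LV output can still follow pulmonary flow. A trivial shunt makes little difference.
- **Planned analysis.** I.2 names the Bland-Altman plot and limits of agreement for LVEF only. For the output differences it plans normality checks, and it adds a regression for proportional bias. The limits calculated above are therefore an illustration for the output comparison.
- **Conclusion about the device.** A reader might infer that the study would wrongly declare automated output unreliable. No acceptance limit is stated, so that does not follow from any rule in the protocol.
- **Frequency.** Nothing in the protocol says how many such patients to expect. Four of 35 would be 11% of the component, and the documents offer no support for it.
- **Inference.** B.1 describes formal echocardiography; that KOSMOS computes output from LV volumes in the same way is implied by the biplane wording in I.2. The reason for excluding regurgitation is not given either.

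It can also be said that handling of special cases belongs in a statistical analysis plan, which is not at hand. But eligibility is fixed in the protocol, and I.2 defines the analysis set with one named exception. A later plan that dropped these patients would contradict it.

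**Conclusion.** The point holds in limited form. As written, D.1, D.2 and I.2 admit and analyse patients with an LV assist device, a percutaneous LV pump or a known haemodynamically significant atrial-level shunt. Their LV-volume output and catheter output can differ even when the device reads correctly, so the stroke volume and cardiac output comparison can charge the device with an error it did not make.

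The direction of the design weakness is clear; its size is not. One patient is 1/35 = 2.9% of the planned evaluable sample. Under the step 4 assumptions with an SD of 0.8 L/min, one or two such patients would widen limits of agreement by 8% to 33%; with none, the effect is zero. For atrial-level shunts the conclusion also depends on the unstated catheterization output method. The LVEF component and both sample size figures are untouched.

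**What to change.** Amend two places, for the stroke volume and cardiac output comparison only.

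- **D.2:** exclude from that comparison patients with an LV assist device or percutaneous LV pump in place at the KOSMOS scan or at the catheterization, and patients with a known haemodynamically significant atrial-level shunt. The investigators should state how significance is judged, as D.2 already does for regurgitation with its severity grade.
- **I.2:** add that any such patient identified after enrollment is omitted from the output comparison, that the number omitted is reported, and that these patients remain in the LVEF analysis.

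Extracorporeal support, right-sided devices and intracardiac shunts in general need not be listed on this argument.

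The cost is about one sentence in each section, applied through the record review that D.2 already plans. Section M speaks of the study in the past tense; if enrollment is complete, the I.2 change still works alone, provided it is settled before the output data are compared. The downside is a few fewer output pairs, taken from the allowance of 70 recruited for 35 evaluable, and a slightly narrower population for the output claim.

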## D.3 Withdrawal of Subjects

1. *Describe anticipated circumstances under which subjects will be withdrawn from the research without their consent:*

As the only intervention in this research study is the performance of a bedside cardiac ultrasound, which will take place as soon as possible after consent has been obtained, we do not anticipate any subjects being withdrawn from the research without their consent. If for some reason the patient’s primary treating physician determines that it is in the patient’s best interests to be withdrawn from the study then they will need to notify they study team, at which point the patient will be removed from the study.

1. *Describe procedures that will be followed when subjects withdraw or are withdrawn from the research, including the possibility of partial withdrawal from study intervention with continued data collection:*

If a participant is withdrawn from the study or chooses to stop being in the study, it will not affect their care or treatment outside this study. Any data collected prior to withdrawal will still be used for the study.

1. *Describe any necessary safety precautions to be applied to subjects who withdraw or are withdrawn (tapering drug doses, evaluative x-ray, etc.):*       or N/A

##

## D.4 Recruitment and Retention

###

### D.4.1 Local Recruitment Methods

Describe the following attributes of the recruitment plan for the local Tufts site:

1. When, where, and how potential subjects will be recruited:

Potential subjects will be screened for potential recruitment by the study investigators This will occur when patients are admitted to the inpatient medical, surgical or intensive care units at Tufts Medical Center and/or when they present to TMC for an echocardiogram and/or right heart catheterization. Once screened for possible inclusion the study team will approach the patient for inclusion in the study.

1. Source of subjects (for example, patient population, local community, etc.): Subjects presenting to TMC for an echocardiogram and/or right heart catheterization and those admitted to TMC.
2. Methods that will be used to identify potential subjects: Physician referral and chart review
3. If print and media advertisements will be used, specify when, where, how long and frequency of the advertisements that will be published/aired:       or  N/A
   1. Check to confirm that any necessary permission will be obtained for posting/airing these (for example, permission to post a flyer on a bulletin board).
4. If recruitment material is being mailed or otherwise distributed, submit the proposed material and describe where/how the distribution list will be obtained:       or  N/A
5. Describe how the recruitment methods described will be effective in attracting the targeted subject population: The target population is patients who recently underwent or are scheduled to undergo an echocardiogram and/or right heart catheterization. By screening patients scheduled for these tests we will be able to efficiently identify potential subjects for recruitment.

### D.4.2 Study-Wide Recruitment Methods

Is this is a multicenter study where subjects will be recruited by methods not under the control of the local Tufts site (e.g., call centers, national advertisements)?

**Yes  No**

If **Yes**, respond to all of the following:

### D.4.3 Payment

Will subjects receive money, gifts, or any other incentive for participating in this study?

This does not include reimbursement for expenses, which is considered in the next section.

**Yes  No**

If **Yes**, respond to all of the following:

### D.4.4 Reimbursement

Will subjects be reimbursed for their expenses, such as travel, parking, meals, or any other study related costs?

**Yes  No**

If **Yes**, respond to all of the following:

1. What qualifies for reimbursement and whether pre-approval is needed:
2. How subjects will be required to document expenses for reimbursement (e.g., provide receipts):
3. How and how often subjects may request reimbursement:
4. How reimbursement will be made (e.g., cash, check, Greenphire ClinCard). Please note, if Greenphire ClinCard will not be used to provide reimbursement, you must use a log to track reimbursements to subjects, as these reimbursements are subject to audit:
5. The reimbursement schedule (when will subjects be reimbursed):

# Costs to Subjects

Does the research involve any costs to subjects?

**Yes  No**

If **Yes**, describe any costs that subjects might be responsible for due to participation in the research:

#

# Study Design

## F.1 Study Timelines

- 1. Describe the duration of an individual subject’s participation in the study:

Participants will be required to allow a Focused cardiac ultrasound be performed at the time of enrollment. Following this study there is no further requirement from the subject. The research team will follow up on the results of the subjects formal echocardiogram and/or right heart catheterization by reviewing the patient’s medical records if it is not available at the time of enrollment. After this information has been collected the subject’s participation will cease.

- 1. Describe the duration anticipated to enroll all study subjects at the Tufts study site:

12 months

- 1. Describe the estimated date for investigators to complete this study (complete primary analyses):

December 2021.

## F.2 Procedures

1. If **Yes**, respond to all of the following:
2. *Describe the scientific, methodological, and medical reasons to use a placebo:*
3. *Describe the care that will be given to subjects who receive placebo. If this is local standard of care, specify that:*
4. *Describe all potential risks to the placebo group and how the risks will be minimized.*
5. *Summarize the research design and sequentially identify all procedures to be performed to accomplish the specific aims of the project. Clearly identify and distinguish procedures that are considered experimental, procedures that are performed exclusively for research purposes (including “extra” routine tests), and procedures that would occur regardless of the research (i.e., standard of care). Point out any procedures, situations, or materials that may be hazardous, and the precautions to be exercised to maintain subject safety:*

This is a prospective cohort study. Consecutive patients cared for at Tufts Medical Center, who have had a recent (within 30 days), or are scheduled to have a subsequent TTE performed at the discretion of the treating team will be screened for participation. Also, patients who are undergoing a right heart catheterization for a clinical indication will also be eligible for recruitment.

We will prospectively collect baseline clinical and demographic characteristics at the time of enrollment. We will be accessing the electronic medical record (Sorian) and entering the information collected into RedCap. There will be no collection of data beyond the date of enrollment, with the exception of those patients whose TTE or right heart catheterization has yet to be performed, in which case the subsequent TTE/right heart catheterization report will be the only information collected prospectively beyond the day of enrollment. The specific procedures to be followed will be:

- Patients who have had a recent TTE (within 30 days), or are scheduled to have a TTE and/or right heart catheterization performed for clinical reasons are eligible to participate in this study.
- If agreeable to participate in the study then participants will receive the usual standard of care (right heart cath and/or TTE) as dictated by the treating medical team.
- Upon signing the consent form, the research team will begin to collect baseline clinical and demographic information about participants from them and/or their medical chart.
- Participants will then undergo the KOSMOS ultrasound evaluation at the time of enrollment or the earliest convenient time after enrolling in the study.
- The TTE and/or right heart catheterization data will be collected and compared with the results of the KOSMOS ultrasound.

*Please also describe the following concerning procedures:*

- - - - 1. How individuals will be screened for eligibility. Specify screening that will take place prior to informed consent and screening that will take place after informed consent:

Screening will begin through identifying individuals who are scheduled to undergo transthoracic echocardiogram and/or right heart catheterization at Tufts medical center. Patients who have recently underwent an echocardiogram may also be included if they are identified by the study team as potentially eligible for participation. There will be no additional screening prior to consent. Following consent the patient’s medical history will be evaluated by questioning the patient and, when necessary, reviewing the patient’s medical records for exclusion criteria. If no exclusion criteria are identified at this point then the patient will begin the protocol as described above.

- - - - 1. Procedures being performed to monitor subjects for safety or to minimize risks:

All data collected will be documented in the case report form in RedCap, which is stored on the Tufts secure server.

- - - - 1. All drugs and devices used in the research, their regulatory approval status, and the purpose of their use:

The KOSMOS device used in this project is an FDA approved ultrasound device that is available for commercial sale. It will be used to perform the bedside cardiac ultrasound as discussed above.

- - - - 1. The source records that will be used to collect data about subjects. (Attach all surveys, scripts, and data collection forms.):

See attached RedCap CRF

1. Is there a placebo control arm?

